## 5.2 Statistical methods

### 5.2.1 General principles

A statistical analysis plan was developed by the biostatistician and the principal

investigator based on the study protocol, and the formative documents were refined before data locking.

The statistical analysis software was SPSS software version 19.0, and the confidence level for all confidence intervals was taken as 95%.

For continuous variables, the number of non-missing subjects, mean, standard deviation, median, minimum and maximum values will be listed. For categorical variables, they will be listed in the form of frequency tables (frequencies and percentages).

### **5.2.2 Principal analysis**

The primary endpoints were the statistical rate of complete pathological remission, and the incidence, severity, association, risk factors, measures taken and their regression for all AEs.

## **5.3 Determination of sample size**

Number of subjects: n=45

The sample size calculation used Simon's two-stage maximum value design. Based on the Checkmate-816 trial, the minimum pCR rate was set at 25%, and the expected pCR rate was 45%. Assuming a type I error rate ( $\alpha$ ) of 0.05 and a type II error rate ( $\beta$ ) of 80%, a sample size of 41 patients was needed. Seventeen patients were enrolled in stage 1. If more than 5 patients achieved pCR, the trial proceeded to stage 2; otherwise, the trial was terminated.

## **6. Adverse event reporting**

### **6.1 Adverse event observation**

An adverse event (AE) is any unfavorable medical occurrence that happens after a subject in a clinical trial has signed an informed consent form, regardless of whether it is causally related to the treatment. AEs can encompass a wide range of unfavorable symptoms, signs, laboratory test abnormalities, or diseases. Specifically, AEs include at least the following:

- 1) A pre-existing medical condition or disease is recorded as an AE only if it worsens after the initiation of study treatment.

2) Any newly occurring AE: This includes any new adverse medical condition (such as symptoms, signs, or newly diagnosed diseases).

3) Abnormal clinically significant laboratory test results that are not attributable to concomitant diseases.

Adverse events that occur during both the pre-treatment and post-treatment phases are also considered AEs according to regulations. Therefore, safety monitoring for AEs or serious adverse events (SAEs) should be reported from the time the subject enters the trial (by signing the informed consent form) until the end-of-trial visit.

## **6.2 AE rating**

AEs are categorized as grade 1-5 according to NCI Classification Criteria for Common Acute and Subacute Toxicities (NCI-CTCAE version 5.0). If the AE is not listed in the NCI toxicity classification criteria, it can be judged according to the following criteria:

1) Grade 1 (mild): no clinical symptoms or mild clinical symptoms; abnormal clinical or laboratory tests only; no treatment required;

2) Grade 2 (moderate): requires minor, localized or non-invasive treatments; age-appropriate limitations in Activities of Daily Living (ADLs), which are defined as cooking, shopping, talking on the phone, counting money, etc;

3) Grade 3 (severe): a serious adverse event (SAE) may include a condition that is severe or has medically significant symptoms but is not currently life-threatening. It can result in hospitalization or prolonged hospitalization, lead to disability, and restrict the individual's ability to perform activities of daily living (ADLs). Self-care ADLs encompass tasks such as bathing, dressing, undressing, eating, using the bathroom, and taking medication, as long as the individual is not bedridden;

4) Grade 4 (severe): Life-threatening and requires urgent treatment;

5) Grade 5 (death): Lethal.

## **6.3 AE record**

Detailed records of the name, severity, time of occurrence, duration, management measures, and resolution of various adverse events (AEs) during the study period will be meticulously documented in the case report form (CRF). Related examinations will

be conducted at least once a week and followed up until normalization or the end of the study. Any adverse events occurring within 30 days of the last dose should be reported and recorded.

## **6.4 Determination of the relationship between AEs and the test drug**

Possible associations between AEs and the test drug were evaluated according to a five-tier classification, including: definitely related, very probably related, probably related, probably not related, and not related.

## **6.5 SAE**

### **(1) Definition of serious adverse event**

A serious adverse event (SAE) refers to medical occurrences during clinical studies that necessitate hospitalization or prolonged hospitalization, result in disability, impact the ability to work, endanger life, or lead to death or congenital malformations. SAEs primarily include the following unintended medical events:

Events that result in death;

Life-threatening events (the term "life-threatening" means that there is an immediate risk of death to the subject at the time of the event/reaction; it does not mean that death may occur only if the event/reaction deteriorates further);

Events that require hospitalization or prolonged hospitalization;

Events that can result in permanent or severe disability/malfunction;

Congenital anomalies or birth defects;

Other important medical events.

### **(2) Pregnancy**

Pregnancy occurring during a clinical study should be reported as SAE.

### **(3) Disease progression**

Disease progression (including signs and symptoms of progression) should not be reported as an SAE. But the death due to disease progression occurring within the trial or safety reporting period should be reported as an SAE. Hospitalization for signs and symptoms of disease progression should not be reported as an SAE. If the final

outcome of the cancer is death within the trial or safety reporting period, then the event leading to death is reported as an SAE.

(4) Perform other anti-tumor therapy

If the subject is initiated on other antitumor therapy, the reporting period for non-death AEs ends with the initiation of the new antitumor therapy. If the death occurs within the SAE reporting period after the end of study treatment, it must be reported regardless of whether the patient receives other treatment.

(5) Hospitalization for treatment

AEs that result in hospitalization or prolonged hospitalization in clinical studies should be considered SAEs. Any initial admission to a healthcare facility (even if shorter than 24 hours) meets this criterion.

Hospitalization does not include the following conditions:

Rehabilitation facilities or convalescent hospital;

Routine emergency room admissions;

Same-day surgery (e.g., outpatient/same-day/ambulatory) Inpatient hospitalization unrelated to worsening of AE or prolonged hospitalization is not an SAE;

Admission for a pre-existing condition with no new AE occurring and no aggravation of the pre-existing condition (e.g., to screen for abnormal laboratory tests that have persisted to date prior to the test);

Hospitalization for administrative or medicare-insured reasons (e.g., routine annual physical examination);

Hospitalization specified by the trial protocol during the clinical study (e.g., operation as required by the trial protocol);

Elective hospitalizations not related to worsening of AE (e.g., elective cosmetic surgery);

Scheduled treatments or surgical procedures should be documented throughout the trial protocol and/or in the individual subject's baseline information;

Hospitalization solely for blood product use.

Diagnostic or therapeutic invasive (e.g., surgery), non-invasive procedures should not be reported as AEs. However, if the disease condition that led to the procedure meets the definition of an AE, it should be reported.

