- [17] Adverse events: recorded from the time of signing the informed consent to 90 days after the last dose. Adverse events should be followed until they disappear, resolve to baseline levels or  $\leq$  grade 1, reach steady state, or are reasonably explained (e.g., lost to follow-up, death).
- [18] Concomitant medications: record drug combination/concomitant treatments within 14 days prior to the first study medication up to the end of the safety visit, and record drug combination/concomitant treatments only for adverse events related to the use of the study drug after completion of treatment with the study drug or withdrawal from the study.
- [19] Safety follow-up: starting after the last study treatment, follow-up visits will be conducted every 30 days ( $\pm 3$  days) until 90 ( $\pm 7$  days) after the last study treatment. The first of these safety visits should be at the study center to complete the examinations and assessments specified in the protocol; subsequent safety follow-ups will be by telephone and will be required only to collect survival information, drug combination/concomitant therapies, and adverse events.
- [20] Survival follow-up: at the end of the safety follow-up period, subjects are entered into survival follow-up until the subject dies, is lost to follow-up, informed consent is withdrawn, or the sponsor terminates the study. During this period, follow-up visits were conducted every 3 months during years 1-2, every 6 months during years 3-5, and annually thereafter to collect survival information as well as information on subsequent treatment.

- [21] Myocardial enzymes test: creatine kinase isoenzyme (CK-MB), alpha-hydroxybutyrate dehydrogenase, creatine kinase, lactate dehydrogenase, etc., once within 7 days prior to randomization as well as pre-dose, pre-operative, post-operative, and safety follow up for the second and third cycle of the drug; supplemental testing will be performed during the study period in the presence of precordial pain, palpitations, and electrocardiographic abnormalities, as well as at the end of the treatment.
- [22] Drug of this study: sintilimab, anlotinib in combination with chemotherapy; see the study dosing section for a detailed description.

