### 3.6.2 Dose adjustment and discontinuation of administration

Anlotinib was discontinued if patients developed haemoptysis. For other grade  $\geq 3$  treatment-related adverse events (TRAEs), anlotinib was reduced to 8 mg, and the dose of chemotherapy was reduced by 25.0% of the last dose. Dose modification of sintilimab was prohibited. Patients experiencing intolerable adverse events that led to a delay or discontinuation of one drug continued treatment with the remaining study drug. Treatment continued until intolerable toxicity occurred or consent was withdrawn. Those who developed progressive disease were permitted to undergo surgery or receive SOC-CRT at the investigator's discretion.

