## **4. Research procedures and data collection**

### **4.1 Data collection program**

The duration of safety data collection spans from the time the patient signs the Informed Consent Form (ICF) until 30 days after the final dose. All adverse events must be documented in the Case Report Form (CRF) from the moment the ICF is signed until the study concludes. The incidence and severity of adverse events will be observed and assessed according to the NCI-CTCAE 5.0 criteria. Each patient will undergo scheduled visits, and specific data will be recorded at various time points during these visits.

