#### (6) SAE reporting procedures

SAEs should be reported from the time the subject signs the informed consent form until the 30th (including) calendar day after the last dose of study drug. If a serious adverse event occurs during the trial, it must be reported to the clinical supervisor and the principal investigator within 24 hours. At the same time, Serious Adverse Event (SAE) Report Form for Clinical Research must be filled out, signed and dated, and immediately reported to the sponsoring organization, the ethics committee of the research unit, CFDA, and the Food and Drug Administration of the region where the investigator is located (either provincial or municipal), in the form of a facsimile transmission.

Information on all SAEs must be recorded on the SAE form. Serious adverse events occurring during the continuation period up to 30 days after the last dose must be reported. SAEs occurring after 30 days of the last dose are generally not reported unless they are suspected to be related to the study drug.

For SAEs, detailed observation and documentation of symptoms, severity, time of occurrence, time to management, measures taken, time and mode of follow-up, and regression should be documented. If the investigator believes that a serious adverse event is not related to the trial drug, but is potentially related to a study condition (e.g., discontinuation of the original treatment, or comorbidities during the course of the trial), this relationship should be detailed in the narrative section of the SAE on the medical record report form. If there is a change in the intensity of an ongoing SAE or its relationship to the subject drug, a serious adverse event follow-up report should be sent to the sponsor immediately. All SAEs should be followed until recovery or stabilization.

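### Section 6.5(4) closes reporting of all non-fatal AEs once other antitumor therapy starts, with no exemption for events suspected to be due to the study drugs, and this contradicts section 6.5(6) and the protocol's other AE windows

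*Protocol*

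**What the plan says.** Section 6.5(4) of the protocol deals with patients who start other antitumor therapy. For them, "the reporting period for non-death AEs ends with the initiation of the new antitumor therapy". Only deaths are protected: a death within the SAE reporting period is covered by "it must be reported regardless of whether the patient receives other treatment".

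The other safety sections set their windows without mentioning this cut-off:

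- Flow chart note [17]: AEs are "recorded from the time of signing the informed consent to 90 days after the last dose".
- Section 4.1: safety data are collected "until 30 days after the final dose", and in the same paragraph all AEs go into the CRF "from the moment the ICF is signed until the study concludes".
- Section 6.1: AEs and SAEs are reported from consent to the end-of-trial visit.
- Section 6.3: "Any adverse events occurring within 30 days of the last dose should be reported and recorded".
- Section 6.5(6): SAEs are reported to day 30 after the last dose. Later SAEs are "generally not reported unless they are suspected to be related to the study drug".

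The protocol also provides the route to other therapy. Under section 3.6.2, patients with progression are "permitted to undergo surgery or receive SOC-CRT at the investigator's discretion". Section 3.6.1 allows standard radiotherapy, with the PI's consent, where surgery is unsuitable.

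**The concern.** AE incidence is a primary endpoint (sections 3.2 and 5.2.2), and section 5.1.1 lists treatment-related AEs, SAEs and drug-related SAEs among the main safety indicators. A reporting stop triggered by treatment acts only on patients who leave the regimen early, chiefly those who progress and go on to SOC-CRT or radiotherapy. Late toxicity of a PD-1 inhibitor or an antiangiogenic agent can first appear after that switch. Section 3.2 names immune-associated pneumonia and haemorrhage as AESIs.

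Two things are at stake. A study-drug-suspected SAE could go unreported because a site followed 6.5(4) rather than 6.5(6). In a study planned at two hospitals, sites applying different sections would also collect different safety data, so the pooled rates would have no single definition.

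**Working it through.** No stated figure depends on this point, so there is none to reproduce, and the sample size is unaffected. The check is a comparison of sections followed by simple day counts.

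**Step 1: a test case.** Count days from the last study dose. A patient progresses and starts SOC-CRT on day 14 (assumed). A new, non-fatal, study-drug-suspected event then begins on day 20 or day 45.

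| Section | Event on day 20 | Event on day 45 |
|---|---|---|
| 6.5(4) | Reporting closed | Reporting closed |
| 6.5(6), if serious | Must be reported | Reportable, because suspected |
| 6.3 | Report and record | Outside window |
| Note [17] | Record | Record |
| 4.1, safety data | Collect | Outside window |
| 4.1, CRF | Record | Record |
| 6.1 | Report | Report, if before the end-of-trial visit |

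For a serious event, 6.5(4) and 6.5(6) give opposite instructions on both days. For a non-serious AESI, 6.5(6) does not apply. The conflict is then with 6.3 and 6.1 on day 20, and with 6.1 on day 45. Note [17] and the CRF rule in 4.1 require recording on both days.

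**Step 2: is this only the 30-day versus 90-day disagreement?** No. Suppose every section used 30 days. Therapy starting on day 14 would still put 30 − 14 = 16 of those days beyond the 6.5(4) cut-off. Choosing one window does not remove the stop.

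**Step 3: days after the cut-off.** The document gives no start day for new therapy, so the start day s is assumed. Days lost are 90 − s for note [17] and max(0, 30 − s) for the 30-day window.

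| s | Of 90 days | Of 30 days |
|---|---|---|
| 14 | 76 (84%) | 16 (53%) |
| 30 | 60 (67%) | 0 |
| 42 | 48 (53%) | 0 |
| 60 | 30 (33%) | 0 |

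These are days in which new non-fatal events would not be reportable under 6.5(4). They are not counts of missed events.

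**Step 4: illustration of patients affected.** Let f be the share of the 45 patients who start new therapy inside the window, and q the share of those whose first relevant AE comes only afterwards. The document gives neither. With f from 5% to 20% and q from 10% to 40%, the undercount is 45 × f × q:

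- Low end: 45 × 0.05 × 0.10 = 0.225 patients (0.5 percentage points).
- High end: 45 × 0.20 × 0.40 = 3.6 patients (8 percentage points).

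The range shows scale only, and applies only if 6.5(4) also governs what enters the database.

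**The case against.** The strongest defence has three parts.

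First, stopping at new anticancer therapy is a defensible convention. In a single-arm study of a regimen's safety, counting pneumonitis that follows thoracic radiotherapy could push rates up. This stands for AEs not suspected to be due to the study drugs, so deleting the rule outright would be a trade-off rather than a correction. It does not explain why suspected events lack an exemption that 6.5(6) provides for late SAEs.

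Second, the rule sits in the SAE section and limits a reporting period, while section 4.1 governs CRF recording and note [19] schedules contacts that collect AEs to day 90. On that reading the data behind the AE rates could be intact. This stands in part: the effect on the endpoint depends on which section governs. It does not remove the conflict, because sections 6.1, 6.3 and 6.5(6) also speak of reporting.

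Third, 6.5(4) may be a specific exception to general windows that need not repeat it. That is possible, but nothing states the order of precedence, and 6.5(6) is equally specific about SAEs.

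A reader might infer more than the text supports:

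- That these patients leave the primary safety endpoint. They do not. AEs before the switch count, AEs already begun are followed (note [17], sections 4.8 and 6.5(6)), and deaths in the SAE period are reported.
- That resected patients are cut off by postoperative therapy. The only such therapy named is adjuvant sintilimab (section 4.5, initial follow-up), a drug used in the trial. Whether it counts as new antitumor therapy is undefined, which is an ambiguity and not a stated exclusion.

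**Conclusion.** The contradiction is established from the text. Section 6.5(4) closes reporting of new non-fatal events at the start of other antitumor therapy, whether or not the study drugs are suspected. Section 6.5(6) requires some of the same events to be reported, and note [17] and sections 4.1, 6.1 and 6.3 do not reflect the cut-off.

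The scope is limited to new non-fatal events after the switch, mainly in patients with progression who receive SOC-CRT or radiotherapy inside the window. For those patients the affected part of the 90-day window is large on any of the assumed start days: 33% to 84% for starts from day 60 back to day 14. The 30-day window is affected only if therapy starts before day 30. The number of such patients, and hence the effect on AE rates, cannot be derived from the document. A fixed downward bias should not be claimed either, because some events after the switch will belong to the new therapy.

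The point should be corrected, chiefly so that study-drug-suspected events are handled consistently. No power or sample-size figure changes.

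**What to change.** 1. Amend 6.5(4) so that study-drug-suspected SAEs and AESIs remain reportable after other antitumor therapy starts. For SAEs this restores agreement with 6.5(6). For AESIs it is a small extension, justified by their place in the primary safety endpoint.
2. For all other AEs, state whether the cut-off limits CRF recording or only reporting, and make note [17] and sections 4.1, 6.1, 6.3 and 6.5(6) say the same.
3. State whether adjuvant sintilimab counts as new antitumor therapy for this rule.
4. Record the start date of new therapy, and tabulate AE rates twice: up to that date and over the full window.

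The cost is protocol wording and one CRF date. Note [19] already schedules contacts to day 90, and note [20] and section 4.7 already collect later treatments, so no visits are added. The small downside is that the full-window table will include some events due to the new therapy. The table ending at the new-therapy date lets the reader separate them.

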#### **3.2 Primary endpoints**

**Efficacy:** Observe the pathological complete response (PCR) rate of resected tumor tissues in postoperative patients

**Safety:** According to NCI-CTCAE version 5.0, closely observe and record the incidence, severity, association, risk factors, measures taken and their regression of all adverse events (AEs); special attention should be paid to AEs of special interest (AESIs), which mainly include immune-associated pneumonia, immune-associated cardiomyopathy, immune-associated endocrine system disorders, hypertension, hemorrhage and proteinuria.

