## 2) Safety

- Incidence of treatment-related adverse events (TRAE);
- Incidence of AEs that resulted in treatment discontinuation and/or early study withdrawal;
- Incidence of SAEs and drug-related SAEs;
- Incidence of deaths;
- Discontinuation of medication for adverse event reasons;
- Changes in vital signs before and after treatment (heart rate, blood pressure, temperature, respiration);
- Changes in whole body physical examination before and after treatment;
- Abnormalities in clinical laboratory tests.

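### The blood-product exemption in Protocol section 6.5(5) is not limited by cause, so a transfusion-only admission for a new or worsened adverse event need not count as an SAE

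*Protocol*

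**What the plan says.** Protocol section 6.5(5) opens with the general rule: "AEs that result in hospitalization or prolonged hospitalization in clinical studies should be considered SAEs". It sets a low threshold for what counts as an admission: "Any initial admission to a healthcare facility (even if shorter than 24 hours) meets this criterion". The SAE definition in section 6.5(1) likewise lists events needing hospitalization as serious.

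Section 6.5(5) then lists what hospitalization does not include. The last entry is "Hospitalization solely for blood product use", with nothing said about why the blood product is needed. Two other entries do carry a condition on cause. One reads "Admission for a pre-existing condition with no new AE occurring and no aggravation of the pre-existing condition". The other exempts elective stays only where they are unrelated to a worsening AE.

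Section 6.5(5) closes with a sentence on procedures: "However, if the disease condition that led to the procedure meets the definition of an AE, it should be reported".

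Section 5.1.1, under Safety, lists "Incidence of SAEs and drug-related SAEs" among the main indicators. Section 3.2 makes safety a primary endpoint covering all AEs and names "hypertension, hemorrhage and proteinuria" among the events of special interest. Section 6.5(6) attaches the 24-hour report and the notices to the ethics committee and regulators to SAEs.

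**The concern.** Anaemia or thrombocytopenia caused by study treatment, if it leads to an admission for transfusion, is an AE that resulted in hospitalization. The general rule makes it serious, and the exemption takes that status away again through the same criterion. The exemption is defined by the treatment given (blood products), not by whether an AE prompted it.

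Two things are at stake for these cases: their place in the SAE and drug-related SAE counts, and the expedited report that only SAEs trigger. The error runs in one direction, because an exemption can lower the SAE incidence but cannot raise it.

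**Working it through.** The protocol states no SAE rate and no transfusion-admission rate, so there is no figure to reproduce. The check is mainly a reading of the text, followed by a sensitivity calculation on assumed counts.

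**Step 1. Apply the rules to one case.** A patient develops treatment-related anaemia after enrolment and is admitted solely for a red-cell transfusion.
- Section 6.5(1) and the opening of 6.5(5): an AE has resulted in admission, so it is an SAE. A stay under 24 hours suffices.
- Exemption list in 6.5(5): the admission was solely for blood products, so it is not a hospitalization and this criterion is not met.
- Closing sentence of 6.5(5): the anaemia is still reported as an AE. This does not restore the serious label.
- Other routes in 6.5(1): death and disability do not apply. The life-threatening route needs an immediate risk of death, which an ordinary transfusion stay need not involve. The important-medical-event route is open but undefined, and rests on judgement.

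**Step 2. Compare the exemptions.** The pre-existing-condition, elective and unrelated-inpatient-stay entries apply only where no AE is new or worsening. The administrative and protocol-specified entries name a cause other than an AE. The blood-product entry does neither.

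**Step 3. Who could be affected.** Inclusion criterion 8 (section 3.5.1) requires haemoglobin of at least 90 g/L and platelets of at least 100 × 10^9/L, with a 7-day restriction on transfusion. A patient later admitted for blood products has therefore most likely worsened since entry. Admission for the protocol's surgery has its own exemption.

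**Step 4. Effect per patient.** Input: planned enrolment of 45 (section 5.3). If a patient's only serious event is a transfusion-only admission, leaving it out lowers the SAE rate by 1/45 = 2.2 percentage points. A patient with another SAE is already counted and changes nothing.

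**Step 5. Sensitivity, with assumed counts and exact (Clopper-Pearson) 95% intervals.**
- True 6/45 = 13.3% (5.1 to 26.8), one patient exempted: reported 5/45 = 11.1% (3.7 to 24.1).
- True 9/45 = 20.0% (9.6 to 34.6), four patients exempted: reported 5/45 = 11.1% (3.7 to 24.1).

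**Step 6. Chance that the issue arises at all.** If a proportion p of patients has such an admission, the expected number is 45p and the chance of at least one is 1 − (1 − p)^45.
- p = 2%: 0.9 expected, chance 0.60.
- p = 5%: 2.25 expected, chance 0.90.
- p = 10%: 4.5 expected, chance 0.99.

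These values of p are assumptions. The protocol supports none of them in particular.

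**The case against.** The strongest reply is that there is no contradiction: a listed exception narrows a general rule, so a site gets one answer, and the exception is a design choice. As a way of reading lists that is fair. But giving the exception priority is exactly what removes the serious label from a treatment-caused transfusion stay, and nothing in the protocol explains why that is intended.

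A second reply is that other entries also lack a limit on AEs, such as rehabilitation facilities and routine emergency-room admissions. This stands: the list follows no uniform pattern. The comparison holds only against the entries that do carry the limit.

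A third reply concerns reach, and it stands in full. A reader might infer that admissions for bleeding drop out, or that the haemorrhage count falls because haemorrhage is an event of special interest. The text does not support this. The exemption covers admissions solely for blood products, so an admission to investigate, observe or control bleeding still counts. Fatal, life-threatening and medically important events stay serious by their own routes. The underlying anaemia, thrombocytopenia or bleed is still recorded and graded, so the all-AE results and the haemorrhage count are unaffected.

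Finally, SAE incidence is one of eight safety indicators in section 5.1.1, and no threshold or stopping rule hangs on it; the stage 1 decision in section 5.3 uses pCR. This limits the consequence but does not remove the under-count.

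**Conclusion.** The point holds in a narrow form. As written, a transfusion-only admission prompted by treatment-related anaemia or thrombocytopenia need not be counted or expedited as an SAE through the hospitalization criterion, despite the general rule in the same subsection. Only the serious label and what follows from it are at risk.

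The size is 2.2 percentage points of SAE incidence per affected patient. This assumes 45 patients in the denominator and no other SAE in that patient. The number of such patients cannot be derived from the document. A reader might suppose 2 to 5 patients, which would give 2/45 = 4.4 to 5/45 = 11.1 points, but that range is only an assumption. Nor does it follow that the combination would look safer overall, since the graded AE and special-interest results do not depend on this exemption.

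**What to change.** In section 6.5(5), reconcile the exemption with the general rule:
- Limit the blood-product entry to planned admissions for a pre-existing condition that has not worsened since consent.
- Add that an admission for transfusion prompted by a new or worsened AE is reported as an SAE.

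This changes reporting only and leaves patient care as it is. It costs one line of text, a few more SAE forms with their expedited reports, and a possibly higher reported SAE rate.
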